### Analysis

We hypothesize that at the unit of randomization, the clinic, patients in the FLOW approach to dissemination will be more likely to share in their treatment decision compared to patients in the traditional dissemination or usual care arms. Qualitative data will be collected to assist in understanding barriers to implementation, to ensure that patients feel that they are partners in the development of the asthma care plan, and to improve the facilitator-led implementation approach over time.

Also, we hypothesize that clinical outcomes in arm 1 will show greater improvement than arms 2 (traditional) or 3 (control). Bivariate comparisons between study arms will be conducted using chi-square test for proportions and *t*-tests (for two group comparisons) or analysis of variance for means, for each of the six outcome measures: patient perception of shared decision making, ED visits, hospitalizations, controller medication use, beta agonist overuse, and use of oral steroids. Changes over time will be assessed using regression models, including the outcome measure as the dependent variable and study arm, time, and a study arm by time interaction term as independent variables to assess differences by intervention and whether changes over time vary by intervention. Analysis over time will employ generalized estimating equations to address correlation between measures at the same practice [24]. Analysis will be conducted using Statistical Analysis System (SAS) (version 9.3).

Principle investigators at each PBRN site will recruit and enroll clinics into the study. As well as explaining the study and randomization process, each site will provide potential practices with information on incentives for providers and practices such as continuing medical education (CME) category 1 credits for participation and up to 20 CME hours for satisfying MOC4 Metric Module for family medicine providers.

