For the purposes of the study, individual participants will be included in a cluster (clinic) by complete enumeration of patients with a diagnosis of asthma. Representatives from each clinic will agree to participate in the study prior to randomization. To ensure that randomization will be non-biased, randomization will occur centrally using a computer-generated algorithm run by the study statistician, who will not be involved in recruitment, data collection, or deployment of the intervention. Clinics will be randomized in groups by PBRN. Once each PBRN reaches its recruitment target, the list of clinics will be inputted into SAS and assignments to one of the three study arms will be generated randomly without replacement using the PROC PLAN procedure. Thereby, allocation to intervention or control group will be concealed from clinics and site PIs prior to full recruitment. Due to the nature of the intervention, which requires active clinic engagement, intervention assignment will be unblinded following randomization.

Sample size was determined using the method of Hayes and Bennett [25] for comparing proportions in clustered randomized trials. We computed the sample necessary to achieve minimum 80% power to test our primary hypothesis that the participatory dissemination strategy will experience greater improvements in patient outcomes compared to traditional dissemination and usual care. A sample size of 10 clinics, with a minimum of 50 patients per clinic, was determined based on preliminary data showing a 7-point decline in the proportion of patients with asthma exacerbation (i.e., ED visit or hospitalization) from 16% to 9% in clinics where the SDM Toolkit was implemented, and a coefficient of variation (*k*) equal to 0.06. To ensure adequate representation of asthma patients during the study period, we approached clinics with at least 75 asthma patients at baseline.

The outcome measure of asthma exacerbation resulting in an emergency department visit or inpatient admission will be determined using Medicaid claims data with the primary diagnosis of asthma (ICD-9 code 493) or a prescription for oral steroids. Misclassification may occur from coding errors but should be non-differential and not vary between the study’s arms since a single source of data will be used for all outcomes (Table 2). National surveillance studies [2] and intervention studies [7,26] have applied asthma ICD-9 codes to administrative data with useful interpretation of outcomes.

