
**Table 2 Tab2:** **Measures for assessment of changes in patient asthma outcomes**

**Outcome**	**Data source**	**Study arms and networks**	**Collection frequency**
Patient perception of shared decision making [7]	Survey question “Who made the decision today?” collected via index cards at arm 1 and 2 practices	Arms 1, 2	Bimonthly
Asthma emergency department visits [27]	Medicaid claims, CHS Asthma Comparative Effectiveness Research Database	Arms 1, 2, 3	Quarterly
Asthma hospitalization rate [27]	Medicaid claims, CHS Asthma Comparative Effectiveness Research Database	Arms 1, 2, 3	Quarterly
Controller medication use	Medicaid claims	Arms 1, 2, 3	Quarterly
Beta agonist overuse [28]	Medicaid claims	Arms 1, 2, 3	Quarterly
Exacerbation requiring oral steroid [27]	Medicaid claims, CHS Asthma Comparative Effectiveness Research Database	Arms 1, 2, 3	Quarterly

Data was obtained from surveys, insurance claims, and research databases.

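### The trial is sized on ED visit or hospitalization, but the definition adds oral steroid prescriptions and the outcome list has no composite, so no test described in the article matches the powered endpoint

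*Protocol article*

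**What the plan says.** The article describes the exacerbation endpoint in three ways.

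- **Sample size (Analysis).** At least 80% power is claimed for "our primary hypothesis that the participatory dissemination strategy will experience greater improvements in patient outcomes compared to traditional dissemination and usual care". The calculation uses the "proportion of patients with asthma exacerbation (i.e., ED visit or hospitalization) from 16% to 9" per cent, 10 clinics with at least 50 patients each, and "a coefficient of variation (*k*) equal to 0.06".
- **Outcome definition (Analysis, next paragraph).** The outcome is named as an exacerbation leading to an ED visit or admission, but it is identified from Medicaid claims "with the primary diagnosis of asthma (ICD-9 code 493) or a prescription for oral steroids".
- **Outcomes to be tested (Analysis; Table 2).** Bivariate tests are planned "for each of the six outcome measures: patient perception of shared decision making, ED visits, hospitalizations, controller medication use", then beta agonist overuse and oral steroid use. Table 2 has the same six, each in its own row. Neither place lists a composite.

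Two further statements bear on the point. The sample size paragraph makes patient outcomes the primary hypothesis. The abstract and the opening of the Analysis section put shared decision making first, and clinical outcomes follow as an additional hypothesis. Misclassification is said to be non-differential "since a single source of data will be used for all outcomes (Table 2"). Yet Table 2 lists a survey for one outcome and, for three others, "Medicaid claims, CHS Asthma Comparative Effectiveness Research Database".

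**The concern.** A power statement is informative only if it describes the test that will be done. Here it describes the proportion of patients with either of two events. The article then widens that outcome in one place and splits it in another. A component has a lower event rate than the composite. A version with steroid prescriptions has a higher one, made up partly of events to which the planning effect of 16% to 9% does not refer.

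The definition would therefore have to be settled later, possibly with claims data in hand and with clinics already unblinded. The unclear rank of shared decision making adds to this, because that outcome is surveyed only in the FLOW and traditional arms.

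**Working it through.** **Inputs from the article:** p0 = 0.16, p1 = 0.09, n = 50 patients per clinic, k = 0.06. The 10 clinics are read as per arm, since 30 clinics are divided equally among three arms. The article does not state alpha, so two-sided 5% is assumed, with 2.5% as a variant for two comparisons.

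**Formulas (Hayes and Bennett, unmatched proportions):**

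- V = p0(1−p0)/n + p1(1−p1)/n + k²(p0² + p1²)
- Clinics per arm: c = 1 + (z_alpha + z_beta)² × V/(p0−p1)²
- Power with c clinics per arm: Phi( |p0−p1| × sqrt((c−1)/V) − z_alpha )

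**Step 1: the plan's own figure.**

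- V = 0.1344/50 + 0.0819/50 + 0.0036 × 0.0337 = 0.002688 + 0.001638 + 0.000121 = 0.004447.
- V/(0.07)² = 0.9076.
- c = 1 + 7.849 × 0.9076 = 8.12, so 9 clinics per arm at two-sided 5%. At 2.5%, c = 9.63, so 10.
- Power with 10 clinics: 0.07 × sqrt(9/0.004447) = 3.149, and Phi(3.149 − 1.960) = 88%. At 2.5%, Phi(3.149 − 2.241) = 82%.

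The stated 10 clinics per arm is reproduced as adequate for the ED-or-hospitalization composite.

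**Step 2: one component alone.** The article gives no separate rates for ED visits or hospitalizations, so the control rates here are assumptions. The relative reduction is kept at 1 − 0.09/0.16 = 44%. There are 10 clinics per arm, n = 50, k = 0.06, two-sided 5%.

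| Assumed control rate | FLOW rate | Power |
|---|---|---|
| 14% | 7.9% | 83% |
| 12% | 6.75% | 77% |
| 10% | 5.6% | 68% |
| 8% | 4.5% | 58% |
| 4% | 2.25% | 32% |

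Worked line for 12%: V = 0.002112 + 0.001259 + 0.000068 = 0.003439; 0.0525 × sqrt(9/0.003439) = 2.686; Phi(2.686 − 1.960) = 77%.

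**Step 3: composite widened with steroids, control rate assumed 30%.**

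- Same absolute difference (30% v 23%): V = 0.008256, and Phi(2.311 − 1.960) = 64%.
- Same relative reduction (30% v 16.9%): V = 0.007432, and Phi(4.567 − 1.960) = over 99%.

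The documents do not say which effect would apply, so they do not determine whether adding steroids raises or lowers power.

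**Step 4: cluster size.** Fifty is a stated minimum, and clinics need at least 75 eligible patients at entry. If 75 per clinic were analysed, composite power would be 97%. A 12% component would have V = 0.001408 + 0.000839 + 0.000068 = 0.002315 and Phi(3.273 − 1.960) = 91%. An 8% component would have V = 0.000981 + 0.000573 + 0.000030 = 0.001585 and Phi(2.638 − 1.960) = 75%.

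**The case against.** The best defence is that this is a condensed article. The abstract names asthma exacerbations first among its evaluation measures. The description of interventions refers to an exacerbation analysis and fixes its population. Both components are on the outcome list, so the full protocol or analysis plan may well derive the composite. The steroid clause may be loose drafting meant for the separate steroid row of Table 2. That limits the claim to the tests described in this article. It does not remove the conflict, because the text printed here defines the outcome in two incompatible ways and lists neither version for testing.

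Some stronger readings are not supported:

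- *The trial is underpowered.* Its arithmetic holds for the composite. Every lower figure rests on an assumed rate, and power is better if more than 50 patients per clinic are analysed.
- *Adding steroids costs power.* This follows only if the absolute difference is held. If the relative reduction is held, power rises.
- *Any of 11 results could be declared the answer, with a 43% false-positive risk.* The count is six outcomes for FLOW v traditional plus five for FLOW v control, and 1 − 0.95^11 = 43%. That requires independent tests, but the contrasts share the FLOW arm and the outcomes are likely to be correlated. The article also does name a primary hypothesis, and multiplicity is commonly left to an analysis plan.
- *The extra database biases the comparison.* The article does not describe that database, and Medicaid claims underlie all five clinical outcomes. What can be said is that the single-source statement disagrees with the table it cites.

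**Conclusion.** The point holds as an internal contradiction. The 80% power claim attaches to the proportion with an ED visit or hospitalization, the definition paragraph adds a steroid prescription to that same outcome, and the article states no test for either version.

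Power for the intended composite is about 88% (82% at a 2.5% level). For a single component it falls below 80% at a control rate of about 12% or less, given n = 50, k = 0.06, a two-sided 5% level and an unchanged 44% relative reduction. With steroids added, the range at an assumed 30% rate is 64% to over 99%, so no direction can be claimed. Confidence is high on the mismatch in the text. The size of its effect on power depends on event rates that the article does not give.

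**What to change.** - Remove the oral steroid clause from the ED/inpatient definition, and keep steroid-treated exacerbation as its own outcome in Table 2.
- Add the ED-or-hospitalization composite to the outcome list and to Table 2 as the primary clinical outcome. State that it is tested for FLOW v traditional and FLOW v control with the GEE model already planned, and label the other clinical outcomes secondary.
- State how the shared decision making hypothesis ranks against it.
- Correct the single-source statement to agree with Table 2: a survey for one outcome, Medicaid claims for the other five, and the CHS database in addition for three of those.

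The composite can be built from ED and inpatient claims that are already planned, so no new data collection is needed. The cost is that the other clinical outcomes lose confirmatory status. A formal testing order for the two contrasts, or restricting the CHS database to sensitivity analyses, would be a design choice and is not needed to remove the contradiction.

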
**Table 2 Tab2:** **Measures for assessment of changes in patient asthma outcomes**

**Outcome**	**Data source**	**Study arms and networks**	**Collection frequency**
Patient perception of shared decision making [7]	Survey question “Who made the decision today?” collected via index cards at arm 1 and 2 practices	Arms 1, 2	Bimonthly
Asthma emergency department visits [27]	Medicaid claims, CHS Asthma Comparative Effectiveness Research Database	Arms 1, 2, 3	Quarterly
Asthma hospitalization rate [27]	Medicaid claims, CHS Asthma Comparative Effectiveness Research Database	Arms 1, 2, 3	Quarterly
Controller medication use	Medicaid claims	Arms 1, 2, 3	Quarterly
Beta agonist overuse [28]	Medicaid claims	Arms 1, 2, 3	Quarterly
Exacerbation requiring oral steroid [27]	Medicaid claims, CHS Asthma Comparative Effectiveness Research Database	Arms 1, 2, 3	Quarterly

Data was obtained from surveys, insurance claims, and research databases.

## Discussion

Variation in primary care clinics and providers makes it challenging to implement new practices and concepts around asthma management such as SDM. Identifying facilitation methods that improve the dissemination of interventions is an important step towards advancing patient outcomes and avoiding preventable ED visits and hospitalizations, while simultaneously reducing overall health-care costs. This study is designed to explore and scrutinize the effectiveness of two different implementation methods in a cluster randomized trial with a control arm. Data collected during the study and assessment of the impact of the dissemination strategies will allow the team to develop a theoretical framework to better describe the underlying mechanism supporting clinic practice change.

The innovative FLOW method of dissemination uses a flexible, participatory approach to implementation [20]. This model has demonstrated adaptability to the varied work environments and patient populations of different practices. Inclusion of the traditional dissemination and passive dissemination control arms provides methodological rigor.

The results of this study will aid in identifying the most effective method of dissemination by testing pragmatic interventions in a real world, practice-based setting. This study has the potential to make significant impacts on asthma management through the use of a shared decision making approach to treatment, and, by leveraging a partnership with the state-wide Medicaid network of practices and the consortium of research networks.

## Abbreviations

AHRQ: Agency for Healthcare Research and Quality
BOAT: Better Outcomes for Asthma Treatment
CBPR: community-based participatory research
ED: emergency department
EMR: electronic medical record
FLOW: facilitator-led participant owned dissemination
IOM: Institute of Medicine
MAPPR: Mecklenburg Area Partnership for Primary Care Research
NCNC: North Carolina Network Consortium
PBRNs: practice-based research networks
SDM: shared decision making
